#### Power analysis and sample size

Our proposed target of 250 enrolled participants (125 per arm) is based on an anticipated attrition rate of 20%. To test the efficacy of the intervention, our sample size calculation was based on mean differences in SBP in our pilot study [42], which demonstrated a 3-month mean change in SBP of 7.5 mmHg (SD = 16.5) between 2 arms randomized 1:1. Assuming that 206 participants (103 per arm) complete all follow-up assessments, we will have 90% statistical power to detect a similar effect size in our ongoing study.

Although we plan to compare CVD scores between the tow study arms, no FRS data specific to the Native Hawaiian population are available. Therefore, we used data from a previous community-based intervention to calculate the necessary sample size. In a 1-year study with a multiethnic sample recruited in medically underserved urban and rural communities (*n* = 195; 59% White, 37% Black, and 4% Hispanic), the biggest changes in FRS were observed at month four [59]. The reported average reduction in FRS varied according to differences in initial risk profiles – for example, 6.0% (SD = 9.9%) for participants at high risk (FRS ≥ 20) and 1.3% (SD = 4.5%) for participants at intermediate risk (20 > FRS ≥ 10). Among study participants, 63% had HTN, with baseline averages of SBP = 146 mmHg and DBP = 82 mmHg, almost identical to the baseline averages in our pilot study (SBP = 146 mmHg, DBP = 86 mmHg). Given a similar mean change in FRS for participants at intermediate risk, a sample of *n* = 206 will provide 80% statistical power to detect a change in FRS of 1.3% (SD = 4.5%) at 6-month follow-up.

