#### Retention and incentive plan

All participants will receive a gift card incentive equivalent to $25 at each data collection visit, with total incentives of $100 for completing all 4 visits. For the wait-list control arm, the fourth payment will be an incentive to start the *Ola Hou* program at month 12. This strategy will ensure that all participants receive the same dollar amount of incentives, thereby avoiding any perception of unfairness – an important consideration in close-knit Native Hawaiian communities. Intervention participants will also receive an ambulatory upper-arm band BP device (valued at $40) to monitor their progress, which they can keep after the study is completed. Wait-list control participants will receive the same device when they begin the intervention. Reminder calls or emails will be made to both intervention and control participants 1 week before each data collection visit, and follow-up calls or emails will be made to allow participants who miss a data collection visit to reschedule. Participants who miss a visit and do not reschedule will be considered dropouts, and study staff will attempt to re-engage them. In our pilot study, these retention strategies successfully retained 87% of participants over a 3-month period. They should be similarly effective over the 12-month period required by the ongoing study [42].

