#### Statistical analysis

For our first two research aims, statistical analyses will be done on an intention-to-treat basis, with differences between study arms in mean changes in SBP and FRS as the primary outcomes. Participant characteristics and rates of recruitment, retention, and intervention fidelity will be summarized by using descriptive statistics. To test the hypothesis that the intervention will lead to significantly more reduction in SBP and FRS relative to the control condition, mean changes in SBP and FRS between baseline and 3-month and 6-month follow-up will be analyzed by independent t-tests between the 2 arms. Analysis of covariance and general linear modeling approaches will then be used to adjust for relevant covariates, such as gender, age, type of community, and baseline SBP and FRS values. Missing values for SBP and FRS at follow-up visits will be imputed by carrying forward baseline observations. If a covariate value is missing, it will be assumed to be missing at random. For sensitivity analyses, mean changes in SBP and FRS of participants who complete follow-up data collection will be analyzed by using a complete case analysis method. A stratified analysis will also be conducted within site or by gender to explore the potential impact of such factors on outcomes. In addition, data collected at all study visits will be modeled by repeated measures analysis of variance and linear mixed effects models, incorporating correlated data from multiple visits, to examine the post-intervention maintenance of SBP and FRS improvements. Determination of the appropriate covariance matrix in the repeated measure analysis will be based on quality of fit to the data by using the method of Fitzmaurice et al. [73]. Statistical analyses will be performed in SAS 9.4 (2015 SAS Institute Inc.). A two-tailed *p*-value <0.05 will be regarded as statistically significant.

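### The 90% SBP power is a completer figure at a count that 20% attrition does not give; the planned baseline-carried-forward analysis has about 84–89% at 20% missing, depending on assumptions the protocol does not fix

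*Protocol article*

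**What the plan says.** Under Power analysis and sample size, the protocol article sets the enrolment target: "Our proposed target of 250 enrolled participants (125 per arm) is based on an anticipated attrition rate of 20" per cent. The planning effect is taken from the pilot, which "demonstrated a 3-month mean change in SBP of 7.5 mmHg (SD = 16.5) between 2 arms randomized 1:1". Power is then given for those expected to finish: "Assuming that 206 participants (103 per arm) complete all follow-up assessments", "we will have 90% statistical power to detect a similar effect size". The same 206 is reused for the Framingham Risk Score (FRS) power statement.

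Under Statistical analysis, for the first two aims, "statistical analyses will be done on an intention-to-treat basis", by two-sample t-tests on change from baseline. For missing outcomes the rule is: "Missing values for SBP and FRS at follow-up visits will be imputed by carrying forward baseline observations". An analysis of those who complete follow-up is planned only as a sensitivity analysis. The test level is fixed by "A two-tailed *p*-value <0.05 will be regarded as statistically significant".

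The Retention and incentive plan reports that in the pilot "these retention strategies successfully retained 87% of participants over a 3-month period" and expects similar effectiveness over 12 months. The pilot section gives mean SBP reductions of 18.3 mmHg (intervention) and 7.6 mmHg (control).

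**The concern.** Two things do not fit together.

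- **The count.** 250 enrolled, 20% attrition and 206 completers cannot all hold.
- **The analysis.** Inflating enrolment for attrition protects an analysis of completers. It does not protect one that keeps every dropout with a change of zero. Carrying baseline forward pulls both arm means towards zero, so the expected difference shrinks in proportion to the missing fraction. The additional participants in the denominator do not fully make up for that.

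The 90% is therefore attached to the sensitivity analysis rather than to the planned main test. Someone reading a null or borderline SBP result would rely on a type II error of 10% that was not calculated for the test in front of them.

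**Working it through.** **Inputs.** Difference 7.5 mmHg, SD 16.5, 1:1 allocation, 250 enrolled (125 per arm), 20% attrition and 206 completers come from the sample-size section. Two-sided 5%, t-test on change and baseline carried forward come from the statistical analysis section. The pilot arm changes and the 87% retention come from the sections named above. Power uses the noncentral t distribution with noncentrality δ / (SD × √(2/n)), n per arm.

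**1. The protocol's own figure.** With n = 103: 7.5 / (16.5 × √(2/103)) = 3.26, power 90.1%. The stated 90% reproduces.

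**2. The completer count.**
- 250 × 0.80 = 200, that is 100 per arm.
- 206 / 250 = 82.4%, that is 17.6% attrition.
- 206 / 0.80 = 257.5, so 258 enrolled would be needed.
- With n = 100: 7.5 / (16.5 × √(2/100)) = 3.21, power 89.2%. The slip costs 0.9 of a point.

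**3. The planned analysis.** Let a fraction r of each arm be observed, with mean change m and SD 16.5, and let the rest have a change of 0. Then:
- expected difference = r × 7.5
- variance in an arm = r × 16.5² + r(1 − r) × m²

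With r = 0.80 the difference is 6.0 mmHg and the variance is 217.8 + 0.16 × m². The variance depends on the mean change in each arm, which the protocol does not fix for this trial. Three assumed pairs, each 7.5 mmHg apart, show the range (n = 125 per arm):

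| Assumed mean change, control / intervention | Arm variances | Pooled SD | Noncentrality | Power |
|---|---|---|---|---|
| 0 / −7.5 | 217.8, 226.8 | 14.91 | 3.18 | 88.7% |
| −7.6 / −15.1 (pilot control change) | 227.0, 254.3 | 15.51 | 3.06 | 86.1% |
| −10.8 / −18.3 (pilot intervention change) | 236.5, 271.4 | 15.93 | 2.98 | 84.3% |

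Simulation of 40,000 trials per case gave 88.6%, 85.8% and 84.4%.

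**4. Other missing fractions, same three pairs in the same order.**
- 17.6% missing (the protocol's 206): difference 6.18 mmHg; power 89.6%, 87.5%, 85.9%.
- 13% missing (the pilot's three-month loss): difference 6.53 mmHg; power 91.3%, 89.8%, 88.7%.

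**5. The planning difference.** The pilot arm means give 18.3 − 7.6 = 10.7 mmHg, not 7.5. Using those means with SD 16.5 and 20% carried forward, the difference is 0.8 × 10.7 = 8.56 mmHg, the pooled SD 15.79 and the power 99%.

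**The case against.** The strongest reply is that the only discrepancy certain from the text is the completer count, which is worth less than one point of power. Everything beyond that rests on assumptions:

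- **Missing fraction.** The protocol does not say over what period the 20% applies. The 206 are those who complete all follow-up, and the retention section speaks of 12 months, whereas the arms are compared at 3 and 6 months. Fewer may be missing then, and at 13% the shortfall all but disappears.
- **Arm means.** Only the 7.5 mmHg gap comes from the sample-size section. The pairs of arm means in the table are constructed.
- **Origin of the 7.5 mmHg.** If the pilot estimate already carried baseline forward, shrinking it again counts the dilution twice. At 7.5 and 16.5 with 125 per arm, power would be 94.7%.
- **Covariate adjustment.** The planned adjustment for baseline SBP may recover some precision.

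All of this stands as a limit on the size of the loss. It does not reconcile 250, 20% and 206, and it does not show that the 90% was calculated for the analysis the protocol makes its main one.

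Two stronger readings are tempting. One is a single figure, such as a flat 86%; that is one row of the table, and the documents do not select it. The other projects the pilot's 13% loss over a second three months (0.87² = 0.757 retained); the retention section states the opposite expectation.

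**Conclusion.** The point holds in a limited form. The three enrolment figures are inconsistent, at a cost of 0.9 of a point (90.1% to 89.2%). The stated 90% describes completers, not the planned intention-to-treat analysis. For that analysis power is about 84–89%, if 20% are missing in both arms at the analysed visit and 7.5 mmHg with SD 16.5 are completer values. It is about 89–91% at 13% missing, and there is no dilution if the pilot's 7.5 mmHg was already a carried-forward estimate.

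A reader might infer that the trial is underpowered for SBP. The documents do not support that: power stays above 80% in every case in the table, and the 10.7 mmHg implied by the pilot arm means would give ample power. What is wrong is the figure as stated and the analysis it is attached to. The unexplained gap between 7.5 and 10.7 mmHg moves power more than the completer count does.

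**What to change.** In Power analysis and sample size:

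1. Reconcile 250, 20% and 206. Either state 200 completers (100 per arm, 89.2%), or keep 206 and state the 17.6% attrition that it implies.
2. Say that the 90% refers to completers.
3. Give power for the planned carried-forward analysis as a range, with the missing fraction and arm changes assumed: about 84–89% at 20% missing. Say whether the pilot's 7.5 mmHg was itself a carried-forward estimate. Alternatively, make a likelihood-based analysis of the observed data primary and quote about 89%, the power of 100 per arm.
4. Reconcile the 7.5 mmHg with the 10.7 mmHg implied by the pilot arm means.

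Do not simply put 200 into the FRS statement. For a two-arm comparison with difference 1.3 and SD 4.5, power is 54.1% at 103 per arm and 52.9% at 100, so the stated 80% reproduces at neither count and needs its own correction.

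The cost is a few sentences and a slightly less favourable power statement if the range is adopted. No extra participants are needed; changing the primary analysis, if that route is chosen, also means revising the statistical analysis section.

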## Methods

### Study design

An overview of the study design appears in Fig. 1. We are conducting a 2-arm RCT using a wait-list control. We will recruit 250 adult Native Hawaiians with confirmed HTN and perform a 1:1 randomization within each study site, such that 125 are assigned to the intervention and 125 are assigned to the wait-list control arm. The hula intervention will be delivered by experienced *kumu hula* and trained community peer educators to groups of 12 to 15 at each study site following standardized protocols. Our primary outcomes are reductions in SBP and improvements in CVD risk as measured by the Framingham Risk Score (FRS). We elected to focus on SBP instead of DBP because the former is a stronger predictor of CVD risk, and its predictive strength increases with age [47–49]. Changes in SBP and FRS from baseline will be compared between study arms at 3-month and 6-month follow-ups. Wait-list participants will be offered the hula intervention after completing their 6-month follow-up. The original intervention arm will also complete a 12-month follow-up to assess the maintenance of SBP and FRS improvements.

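### The 80% power stated for the Framingham Risk Score does not follow from its own inputs: the planned two-arm test with 103 completers per arm has about 54%

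*Protocol article*

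**What the plan says.** The Statistical analysis section names "differences between study arms in mean changes in SBP and FRS as the primary outcomes". Changes from baseline to 3 and 6 months "will be analyzed by independent t-tests between the 2 arms", and "A two-tailed *p*-value <0.05 will be regarded as statistically significant". Covariate-adjusted models come after the t-tests. Study design specifies that the trial will "perform a 1:1 randomization within each study site".

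The Power analysis and sample size section sets the numbers: "Assuming that 206 participants (103 per arm) complete all follow-up assessments", from 250 enrolled. For SBP it takes a between-arm difference of 7.5 mmHg (SD 16.5) from the pilot and states 90% power.

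For FRS it says that no data specific to Native Hawaiians are available. It turns to an earlier one-year community intervention, where "the biggest changes in FRS were observed at month four". The average reduction reported there was 6.0% (SD 9.9%) in high-risk participants and "1.3% (SD = 4.5%) for participants at intermediate risk (20 > FRS ≥ 10"). Using the intermediate-risk figures, it concludes that 206 participants "will provide 80% statistical power to detect a change in FRS of 1.3% (SD = 4.5%) at 6-month follow-up". The paragraph opens by saying that CVD scores will be compared between the two arms, so the calculation is offered in support of that comparison.

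**The concern.** The FRS standardised difference (1.3/4.5 = 0.289) is well below the SBP one (7.5/16.5 = 0.455), yet the same 206 people are said to give 80% power for the first and 90% for the second. These cannot both come from the same two-arm test.

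FRS is a primary outcome and the whole of Aim 2, and the Discussion relies on it for the clinical meaning of any SBP effect. If the power is overstated, a non-significant FRS result could be taken as stronger evidence of no effect than the design can supply.

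A second point concerns the input. The 1.3 is described as an average reduction within a risk stratum. The trial's contrast is intervention change minus control change.

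**Working it through.** **Inputs, all from the protocol article**

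- Test: two-sample t-test on change, two-sided alpha 0.05 (Statistical analysis).
- Analysed: 103 per arm, 206 in total (Power analysis and sample size).
- FRS: difference 1.3, SD 4.5, stated power 80% (same section).
- SBP: difference 7.5, SD 16.5, stated power 90% (same section).

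**Formula.** Standard error of the difference SE = SD × √(2/n), with n per arm. Noncentrality = difference / SE. Power is the probability that a noncentral t with 2n − 2 degrees of freedom falls beyond the two-sided critical value, which is 1.972 for 204 degrees of freedom.

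**Step 1: reproduce the SBP figure.** SE = 16.5 × √(2/103) = 2.299. Noncentrality = 7.5/2.299 = 3.262. Power = 90.1%, and 103 is the smallest number per arm that reaches 90%. The method matches the protocol's own SBP calculation.

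**Step 2: the FRS figure by the same method.** SE = 4.5 × √(2/103) = 0.627. Noncentrality = 1.3/0.627 = 2.073, barely above the critical value. Power = 54.1% (54.5% by the normal approximation).

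**Step 3: what 80% would take.**

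- Detectable difference at 103 per arm: 1.77, and 1.77/1.3 = 1.36, so 36% larger than stated. The normal approximation gives (1.960 + 0.842) × 0.627 = 1.76.
- Completers per arm for a difference of 1.3: 190 (normal approximation 189).
- SD of change at which 1.3 would have 80% power with 103 per arm: about 3.3 instead of 4.5. That means about 45% of the variance explained by covariates, since 1 − (3.33/4.5)² = 0.45.

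**Step 4: can another reading give 80%?** Difference 1.3 and SD 4.5 unless noted.

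| Reading | Power |
|---|---|
| Planned test, 103 per arm | 54.1% |
| 100 per arm (250 less 20%) | 52.9% |
| 125 per arm, everyone followed up | 62.4% |
| 125 per arm, 80–82% completing, baseline carried forward | 53–54% |
| 103 per arm, one-sided 0.05 | 66.3% |
| 125 per arm, everyone followed up, one-sided 0.05 | 73.7% |
| Within-group change, all 206 | 98.5% |
| Within-group change, one arm of 103 | 82.7% |
| 206 per arm | 83.3% |
| High-risk inputs (6.0, SD 9.9), 103 per arm | 99.1% |

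The nearest are a before-after test in one arm and a two-arm test with twice the planned completers. Neither is the planned analysis. The document does not show how the 80% was obtained, so its origin cannot be settled.

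**Step 5: sensitivity to change in controls.** Taking 1.3 as the between-arm difference assumes no mean change in controls. Yet all participants take the 3-hour hypertension course, and the pilot's wait-list group fell by 7.6 mmHg in SBP, which is an input to FRS. As an illustration only, if controls improved by 0.3 points the difference would be 1.0 and power about 35%.

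**The case against.** The strongest case on the other side is that the 54% rests on one pair of inputs. Eligibility is not limited to intermediate risk, and the high-risk figures give 99% power. Suppose, as an assumption, that the sample held only these two strata and controls did not change. Then 10%, 20% and 30% high-risk participants would give about 65%, 74% and 82%. Low-risk participants would pull this down, and the mix is not known. This stands as a caution: 54% is the power for the stated inputs, not a forecast for the trial. It does not rescue the sentence, which names 1.3 and 4.5 as its basis.

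Baseline adjustment could also raise power. But the covariate models follow the t-tests, and no correlation is given to support the 45% of variance that would have to be explained.

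The sentence speaks loosely of a change, which might mean a change within groups. With the stated 206 that gives 98.5%, so it does not yield 80% either.

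The design of the earlier study is not described, so whether 1.3 was strictly within-group cannot be confirmed from this document. What can be said is that the protocol does not present it as a between-arm difference. The arithmetic does not depend on this.

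Finally, the efficacy sample size rests on SBP, and that figure is right. This limits the consequence to the FRS claim.

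**Conclusion.** The concern holds. For the planned between-arm t-test with 103 completers per arm, two-sided 0.05, a difference of 1.3 and an SD of 4.5, power is 54%, about 26 percentage points below the stated 80%. The probability of missing a true difference of that size is 46% rather than 20%. Every input to this result is stated in the protocol, and the method reproduces its SBP figure. No reading of the planned design gives 80%.

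The 54% is conditional on 1.3 being the true difference between arms. It falls if controls improve, and it could rise if many participants are at high risk or if baseline values explain much of the variance. A wrong power figure for a primary outcome must be corrected.

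**What to change.** Replace the last sentence of the power section with wording such as: 206 completers (103 per arm) give about 54% power for a between-arm difference in FRS change of 1.3 (SD 4.5) at 6 months, and 80% power for a difference of about 1.8, using a two-sided t-test at 0.05.

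State that 1.3 is the average reduction reported for intermediate-risk participants in the earlier study, and that using it as a between-arm difference assumes no change in controls. If the sponsor relies on a mix of risk strata or on baseline adjustment to justify a higher figure, the assumed mix or correlation should be written down with the resulting power.

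That is enough. FRS may stay primary with the corrected figure; placing it as a key secondary outcome after SBP is an option, not a requirement. The cost is a change of wording in the protocol and analysis plan and one less favourable number. No added enrolment, visits or data are called for.

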#### Resource sharing and dissemination plan

This study will include data from approximately 250 participants with hypertension, recruited over a period of 4 years. All investigators are aware of and agree to abide by the principles for sharing research resources, as described by the National Institutes of Health (NIH) in “Principles and Guidelines for Recipients of NIH Research Grants and Contracts on Obtaining and Disseminating Biomedical Research Programs." The final dataset will include self-reported demographic, survey, and clinical data.

Sharing of data generated by this project is an essential part of our proposed activities and will be carried out in several different ways. We will make our results available both to the community partners, community members, and scientists interested in our study. Our plan includes presentations at each community site, local and international cultural gatherings, as well as scientific conferences and meetings. We plan to publish our results in scientific peer-reviewed journals following the aforementioned presentations and approval from our community investigators. All publications generated from this project will include community members as contributing authors.

## Discussion

The principal strength of our ongoing intervention study is the use of hula, a popular cultural practice, as the basis of a program to prevent CVD in Native Hawaiians with HTN. Preliminary data strongly support this culturally sensitive approach. Our study is designed to link statistically significant changes in SBP with 10-year CVD risk, a clinically meaningful outcome. Provided the intervention has a significant positive effect, we will be able to explain how the *Ola Hou* program leads to reductions in SBP among Native Hawaiians through our analysis of important psychosocial and cultural mediators.

Our choice of an RCT with a wait-list control design ensures that we have a control condition to enable causal inference while providing all participants with an opportunity to receive the hula intervention. Although this experimental approach is not the most robust among RCT designs, it is acceptable to Native Hawaiians and has been used successfully in past studies with their communities [60]. We anticipate that our study findings will inform future investigations of other traditional cultural dances. Such investigations can evaluate their promise as intervention strategies for reducing CVD risk in indigenous populations in the U.S., Canada, New Zealand, and Australia.

Our study introduces several innovations. Using hula to prevent CVD is a novel approach in the context of contemporary prevention paradigms. Current strategies to prevent CVD are not consistent with Native Hawaiian values and preferences, because they focus on the individual, provide physical activity regimens that are irrelevant to indigenous culture, and are difficult for Native Hawaiians to access or sustain. Instead of culturally adapting an existing Western, evidence-based intervention, we chose a popular traditional Native Hawaiian practice as the basis for our program. The popularity and cultural relevance of hula mean that the *Ola Hou* program can be easily adopted and sustained in any community where Native Hawaiians live, whether in Hawai‘i or elsewhere.

Our outcome analyses will also include FRS, which have strong predictive power for 10-year CVD risk [78, 79]. These risk scores will include data on SBP and other major determinants of CVD risk, including lipid levels, smoking status, gender, and age [57]. These data will enable us to ascertain the longer-term clinical significance of our intervention within our 5-year study period.

Another innovation of this study is our analysis of psychosocial and sociocultural constructs (e.g., cultural identity, perceived ethnic discrimination) that might mediate the intervention effect on BP control. Our pilot study found that the intervention reduced perceptions of racism, and preliminary findings of other ongoing studies indicate that Native Hawaiian ethnic identity is positively related to behavioral and emotional self-control. Thus, our design responds to a transdisciplinary call for studies of the mechanisms underlying behavioral interventions [80–82].

Our ongoing study also has limitations. First, implementing the intervention at several different sites makes it difficult to ensure the consistency in delivery required by standardization, and might therefore introduce confounders into our analyses. To minimize this possibility, we will conduct fidelity checks and offer booster training sessions as needed. Second, we rely on self-report measures for many variables of interest, potentially introducing biases involving recall and social desirability. Nevertheless, self-report is the primary method of assessing attitudes, beliefs, and other cognitive processes, and we will use measures validated in previous studies with Native Hawaiians to minimize self-reporting biases. Third, we anticipate that more women than men might participate, since dancing might be more attractive to women. Accordingly, we will make special efforts to recruit Native Hawaiian men to achieve balanced gender representation.

